## Abstract

**Background:**

A weak referral system combined with limited diagnostic facilities is among the key systemic barriers to the early detection of breast cancer. Strengthening patient pathways is essential to improve follow-up and reduce delays in cancer diagnosis and care. This study aims to assess the effectiveness of the DINKNESH referral and follow-up app, a digital, app-based patient referral system linking early detection of breast-related abnormalities at primary healthcare settings with diagnostic facilities in Ethiopia.

**Methods:**

A two-arm cluster randomised trial with an embedded qualitative study is being conducted at eight primary health facilities and affiliated satellite hospitals in Ethiopia. The study includes women aged ≥18 years presenting with breast abnormalities, as well as women aged ≥30 years with positive findings on clinical breast examination. In intervention cluster facilities, the referral process for further diagnosis is supported by the DINKNESH referral and follow-up app, which facilitates patient registration, data transfer, and reminder services. This is compared with the routine paper-based referral process in the control clusters. The primary outcome is the proportion of completed referrals. All outcome measures will be analysed using IBM SPSS Statistics 25.0. A mixed-effects logistic regression model will be applied, adjusting for potential confounders and accounting for clustering at the facility level. At the end of the intervention period, qualitative interviews will be conducted using the RE-AIM framework to explore the acceptability, challenges, sustainability, and scalability of the intervention.

**Discussion:**

This study will provide robust evidence on whether app-based referral systems for women with breast symptoms can improve follow-up and facilitate early breast cancer detection in low-resource settings such as Ethiopia. The findings will support the WHO Global Breast Cancer Initiative’s goal of diagnosing more than 60% of breast cancer cases at an early stage.

## Administrative information

Note: The numbers in curly brackets throughout this protocol refer to SPIRIT checklist item numbers. The order of the items has been modified to group similar content areas (see http://www.equator-network.org/reporting-guidelines/spirit-2013-statement-defining-standard-protocol-items-for-clinical-trials/).

## Introduction

### Background and rationale {6a}

With an estimated 2.3 million new cases, female breast cancer is the most commonly diagnosed cancer worldwide [1]. Between the mid-1990s and mid-2010s, breast cancer incidence rates in sub-Saharan Africa increased by more than 5% annually, accompanied by high mortality rates in these regions [2]. In low- and middle-income countries, many women are diagnosed at later stages [3].

In Ethiopia, breast cancer is one of the leading causes of cancer-related death, accounting for an estimated 9061 (22.6%) deaths annually [1]. A systematic review revealed that the rate of early breast cancer diagnosis stands at 34.2%, which is far below the 60% target set by the Global Breast Cancer Initiative (GBCI) [4, 5]. A similar study conducted across 17 sub-Saharan African countries, including Ethiopia, reported a median rate of late presentation of 74.7% [6].

Health system-related barriers to early detection of breast cancer in Ethiopia include frequent misdiagnosis at initial contact, long waiting times for diagnostic tests, limited oncological services and infrastructure across healthcare levels, and a weak referral system [7–9].

Ethiopia’s health system is structured in three tiers. The primary level includes primary hospitals, health centres, and health posts. The secondary level comprises general hospitals, which serve as referral facilities for primary hospitals. The tertiary level consists of specialised referral hospitals. Primary healthcare settings are the first point of contact for patients and play a crucial role in both disease prevention and treatment [10].

There is an absence of clear communication protocols and a lack of a formal referral linkage system in Ethiopia [9]. A study in Tanzania revealed that among referred patients with breast abnormalities who underwent a clinical breast examination (CBE), only 52% had a completed referral [11]. A study in Mexico found that women often did not proceed to the next point of referral because of a lack of access to care, an issue compounded by a referral process described by the women as exhausting [12].

For a successful continuum of cancer care, early detection of abnormalities must be linked to timely confirmed diagnosis and prompt treatment. An effective and efficient referral system requires coordination, communication, and feedback mechanisms at all levels, supported by an integrated information recording system [13].

Recent innovations in e-health, such as the digitalisation of patient registries, have improved referral efficiency in underserved communities [14]. E-referrals enhance communication between primary care providers and specialists, increasing the quality of referrals while minimising unnecessary ones. Studies also show that they reduce missing or incomplete information, thereby streamlining the referral process [15, 16].

Given the burden of breast cancer, low socioeconomic status, limited infrastructure, scarcity of advanced cancer care facilities, and weak health system in Ethiopia, there is a need to develop and test contextually appropriate and feasible interventions. These should aim to improve early detection by identifying breast-related abnormalities and ensuring coordinated referrals at the primary healthcare level. This study aims to use the DINKNESH referral and follow-up app within primary healthcare to facilitate referral pathways for women undergoing a CBE, as well as to evaluate the effects of this intervention on improving referral pathways and the early detection of breast abnormalities, including cancer. The evidence gathered will support policymakers in integrating electronic approaches into cancer care and may serve as a model for addressing other health concerns.

## Objectives {7}

The primary objective of this study is to evaluate the effectiveness of the DINKNESH referral and follow-up app in enhancing referral completion for women with breast-related abnormalities at primary healthcare settings in Ethiopia, specifically by determining the proportion of successfully completed referrals.

Hypothesis: The use of the DINKNESH referral and follow-up app will increase the proportion of completed referrals from 52% to 70% for women with breast-related abnormalities after undergoing a CBE compared with the routine standard referral process.

## Trial design {8}

This is a parallel, two-arm, superiority cluster randomised controlled trial with an embedded qualitative study. The study includes two arms: an intervention arm and a routine standard care arm (Fig. 1).

**Fig. 1 Fig1:**
[figure not shown]
CONSORT diagram of e-health–supported referral of patients with breast abnormalities at primary healthcare facilities in Ethiopia

## Methods: participants, interventions, and outcomes

### Study setting {9}

The study is being conducted at eight primary healthcare facilities (clusters) across three regions of Ethiopia: Oromia, Central Ethiopia, and South Ethiopia and their associated referral hospitals. These facilities were deliberately selected based on prior research and background data because they offer adequate early detection capacity and provide a solid foundation for this interventional study [7, 17, 18]. Each primary healthcare facility is linked to a referral hospital for onward patient referrals.

### Eligibility criteria {10}

Health facilities included in the study are part of the oncology research network supported by the Else Kröner Cancer Center and the DINKNESH Project. Facilities were selected based on their established referral linkages with satellite hospitals. These project sites offer cervical and breast cancer screening, diagnostic, and treatment services.

#### Inclusion criteria

Women aged ≥18 years presenting with a self-reported breast-related abnormalityWomen aged ≥30 years visiting the health centre outpatient department who are willing to undergo CBE and have an abnormal clinical finding (based on the recent Ethiopian breast cancer guideline [19])

#### Exclusion criteria

Women who will not undergo CBEMen (because of the low number of such patients in the study setting)

### Who will take informed consent? {26a}

Trained data collectors are responsible for obtaining informed consent for trial participation. Women who can read and write will provide written consent themselves. In cases where women cannot read or write, a witness will sign the consent form on their behalf to confirm their participation in the trial.

### Additional consent provisions for collection and use of participant data and biological specimens {26b}

Not applicable: This study does not involve the collection or use of biological specimens.

## Interventions

### Explanation for the choice of comparators {6b}

The control arm represents routine standard care. This involves women presenting at health facilities with or without breast-related abnormalities. A health professional trained in CBE will examine the woman and perform the CBE. Based on the findings, the professional will either recommend treatment or initiate a referral for further management. The woman will be given a referral paper, which she must take to the next facility. Upon her visit to the receiving facility, feedback will be sent back to the referring facility.

### Intervention description {11a}

Intervention/DINKNESH referral and follow-up app:

The proposed intervention in this study is the implementation of a digital, app-based referral and follow-up system called the DINKNESH referral and follow-up app—at primary care settings in peripheral regions of Ethiopia.

#### Intervention development

Following a review of the literature, situational assessments, previous studies at the selected sites, and stakeholder discussions, the principal investigator ([name]) and the research team analysed the patient care pathway and developed an algorithm for the DINKNESH referral and follow-up app [20]. Key variables to be documented using the app were identified through literature reviews, expert consultation, and consultative meetings held in close collaboration with the Ethiopian Ministry of Health and regional focal persons for cancer and non-communicable diseases. The app developer, IWKET Plc., provided technical support by creating the mobile application based on the algorithm and selected variables, and continues to offer information technology support as needed.

The development process involved several key stages. Initial stakeholder meetings were held with the Ministry of Health, regional and woreda health offices, service users, and non-governmental organisations experienced in implementing electronic health interventions in Ethiopia. These meetings informed the app’s implementation strategy, drew on lessons from past initiatives, and explored integration into existing systems. A draft prototype was pretested to assess usability, functionality, and potential challenges; necessary revisions were made accordingly. A final stakeholder meeting confirmed that the app was ready for implementation.

#### How does the intervention (DINKNESH referral and follow-up app) work?

Women with self-reported or newly detected breast abnormalities identified through CBE will be registered in the DINKNESH referral and follow-up app. Health professionals at the study sites will use the DINKNESH referral and follow-up app as a communication hub. The app will electronically record patient information, send appointment reminders to patients, and provide advance notifications to receiving facilities with relevant details. It will facilitate referrals through automated messages and continuous information exchange.

### Criteria for discontinuing or modifying allocated interventions {11b}

Because the DINKNESH referral and follow-up app intervention poses minimal to low risk, it may be discontinued at the request of the participant. In the event of discontinuation, the reason will be documented.

### Strategies to improve adherence to interventions {11c}

Several strategies are being implemented to ensure sufficient patient flow and high-quality health services. Given the nature of the study, these strategies aim to increase the number of women with breast abnormalities who seek care at health facilities and are referred, allowing for evaluation of the app’s effectiveness in facilitating complete referrals. Activities include strengthening health professionals’ ability to correctly advise women with breast-related abnormalities and make appropriate referrals according to the recommended guidelines. Training is provided on the CBE, implementation of the DINKNESH referral and follow-up app, community sensitisation, and basic orientation for health extension workers. Health extension workers at the study sites receive orientation on breast cancer and breast cancer screening. During their routine household visits, they inform community members about the availability of CBE services at the health centre.

### Relevant concomitant care permitted or prohibited during the trial {11d}

Standard routine primary healthcare, including CBE and routine referrals, is permitted. However, the use of alternative digital referral systems and any additional referral-focused interventions outside of routine care is prohibited.

### Provisions for post-trial care {30}

Following the trial, the control group will receive training on the DINKNESH referral and follow-up app after any necessary modifications have been made based on the trial findings.

### Outcomes {12}

Primary outcome: Proportion of successfully completed referrals.

Definition of primary outcome: A successfully completed referral is defined as a case in which, after study inclusion, a patient initiates the first diagnostic or treatment procedure at the receiving external institution and feedback is received by the referring institution within 60 days of the referral.

Secondary outcomes:Time from initial presentation at the health facility to first diagnosis for women with breast-related abnormalitiesProportion of internal referrals within the facilityProportion of breast cancers detected at an early stage

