### Participant timeline {13}

Following randomisation, eligible participants visiting the study health facilities are being enrolled (Table 1). In the intervention arm, referral details are being registered and tracked through the DINKNESH referral and follow-up app. Feedback is being recorded upon the patient’s arrival at the referral facility, marking the end of the participant’s study period. In the control arm, referrals are following routine care procedures, and medical records are being reviewed 60 days after referral to assess diagnosis and feedback. The 60-day cutoff for each study participant is based on GBCI recommendations for timely diagnosis [5].

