### Implementation {16c}

The DINKNESH referral and follow-up app is hosted on a secure server at Addis Ababa University. Sixteen health professionals, two per facility, have been trained and will be responsible for using the app to manage referrals based on eligibility criteria and their clinical decisions. Tablets with the DINKNESH referral and follow-up app installed will be provided to the trained health professionals at each facility. At the primary healthcare facilities, the tablets will be given to professionals working in the outpatient department. At the referral hospitals, nurses working in the surgical outpatient department will be responsible for using the app to receive referrals.

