## Data collection and management

### Plans for assessment and collection of outcomes {18a}

#### Primary outcome (proportion of complete referrals)

For the intervention group, the referral status will be digitally recorded. Time intervals from the woman’s initial visit to the facility to when the referral is sent and when feedback is received will be used to calculate the proportion of complete referrals. In the control group, referrals will be managed through routine paper-based procedures. Sixty days after the referral, trained data collectors will review medical records at both the sending and receiving facilities to determine whether feedback was received. The use of a standardised data extraction tool, aligned with the variables used in the DINKNESH referral and follow-up app, will ensure comparability between the two groups.

To further explain the outcome variable, baseline data will be collected from both groups after consent, including sociodemographic information, clinical data, and knowledge of breast cancer. The African Women Awareness of CANcer (AWACAN) tool will be used to assess awareness, health-seeking behaviour, and perceptions. This baseline information will help interpret the primary outcome [23].

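### The primary outcome merges procedure start with feedback, which the app channels in one arm only, so a positive result will be ambiguous unless procedure start is also analysed alone

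*Protocol article*

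**What the plan says.** Outcomes {12} defines the primary outcome as a conjunction: "a patient initiates the first diagnostic or treatment procedure at the receiving external institution and feedback is received by the referring institution within 60 days", counted from referral. The listed secondary outcomes are time from presentation to diagnosis, internal referrals, and early-stage cancers. None counts procedure start without feedback.

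The section on how the app works says that it will "send appointment reminders to patients, and provide advance notifications to receiving facilities with relevant details", and adds: "It will facilitate referrals through automated messages and continuous information exchange". Under Implementation {16c}, at the referral hospitals "nurses working in the surgical outpatient department will be responsible for using the app to receive referrals". In the control arm, Explanation for the choice of comparators {6b} has the woman carry a referral paper, with feedback returned by a route that is not specified; Plans for assessment {18a} calls the control process paper-based.

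Ascertainment also differs. Plans for assessment {18a} states: "For the intervention group, the referral status will be digitally recorded". For controls, 60 days after referral, "trained data collectors will review medical records at both the sending and receiving facilities to determine whether feedback was received". Participant timeline {13} says of the intervention arm: "Feedback is being recorded upon the patient’s arrival at the referral facility, marking the end of the participant’s study period".

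The Abstract's Discussion states the intended conclusion: "This study will provide robust evidence on whether app-based referral systems for women with breast symptoms can improve follow-up and facilitate early breast cancer detection".

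**The concern.** One half of the endpoint is what the trial wants for the woman: she starts a diagnostic or treatment procedure. The other half is a message between institutions, and the intervention is a system for carrying such messages. The article's own rationale is that communication between facilities is weak in routine care, so a difference in feedback between arms is to be expected whether or not attendance changes.

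If the composite differs, the primary analysis cannot say which half moved. Only a gain in procedure start bears directly on women reaching diagnosis, and the intended conclusions concern follow-up and early detection.

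**Working it through.** **The plan's own figure.** Inputs from Sample size {14}: 52% versus 70%, 80% power, 5% significance (taken as two-sided), ICC 0.01, 8 clusters.

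- Per arm, unpooled: (1.960 + 0.842)² × (0.52×0.48 + 0.70×0.30) / 0.18² = 7.849 × 0.4596 / 0.0324 = 111.3, so 222.7 in total. The plan has 222.
- Design effect at 222/8 = 27.75 per cluster: 1 + 26.75×0.01 = 1.2675. Then 222 × 1.2675 = 281.4, rounded up to 282. The plan's figure reproduces.

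**Splitting the endpoint.** Let p be the proportion starting a procedure within 60 days and f the proportion of those for whom feedback also arrives in time. The endpoint rate is p × f. Set p equal in both arms, so that the app brings no additional woman to a procedure, and ask what f must be to give 52% and 70%:

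- p = 0.70: control 0.52/0.70 = 74.3%; app 0.70/0.70 = 100%
- p = 0.80: control 65.0%; app 87.5%
- p = 0.90: control 57.8%; app 77.8%

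Any common p of 70% or more allows the whole 18-point effect to come from feedback. Below 70% it cannot, because the app arm's composite cannot exceed p.

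**Chance of a significant result in favour of the app.** With 4 clusters of 35 per arm, the design effect is 1 + 34×0.01 = 1.34 and the effective n per arm is 140/1.34 = 104.5. Power is Φ{[d − 1.96√(2p̄(1−p̄)/n)] / √[(p₁(1−p₁) + p₂(1−p₂))/n]}, where d = p₂ − p₁ and p̄ is the mean of the two rates. For 0.52 versus 0.70 this is Φ[(0.18 − 0.1323)/0.0663] = Φ(0.72) = 0.76.

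The article gives no feedback or procedure-start rates, so every p and f below is an assumption:

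| p, both arms | f control | f app | Endpoint, control v app | Chance |
|---|---|---|---|---|
| 70% | 74.3% | 100% | 52.0% v 70.0% | 0.76 |
| 70% | 80% | 100% | 56.0% v 70.0% | 0.56 |
| 70% | 90% | 100% | 63.0% v 70.0% | 0.19 |
| 70% | 70% | 95% | 49.0% v 66.5% | 0.73 |
| 52% | 80% | 100% | 41.6% v 52.0% | 0.32 |
| 52% | 90% | 100% | 46.8% v 52.0% | 0.11 |
| 80% | 80% | 100% | 64.0% v 80.0% | 0.73 |
| 80% | 90% | 100% | 72.0% v 80.0% | 0.27 |

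With a t reference on 6 degrees of freedom (8 clusters less 2), the first three rows become 0.62, 0.43 and 0.15. With equal feedback in both arms the chance is the nominal 0.025, as it would be in every row on procedure start alone.

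**Ascertainment.** The definition needs a procedure to have started. Participant timeline {13} ends an intervention woman's study period when feedback is recorded on arrival, which may precede any procedure. Plans for assessment {18a} builds the intervention-arm outcome from the times of visit, referral and feedback and names no procedure date. It describes the 60-day check of records at both facilities for controls only. As written, procedure start may not be captured comparably in the two arms.

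**The case against.** Four points on the other side carry weight.

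- **Feedback belongs to the construct.** The objective is referral completion, and the Introduction lists feedback among the requirements of an effective referral system. Including it is a reasoned choice. This stands, and is why the composite should remain primary.
- **A feedback-free 60-day analysis is already planned.** Statistical methods {20a} splits time to diagnosis at 60 days and uses mixed-effects logistic regression with facility clustering. An effect confined to feedback should show there as no difference. This stands in part: the clock runs from first visit rather than referral, a confirmed diagnosis is required rather than a started procedure, and the data come from the app in one arm and medical records in the other.
- **The size is assumed.** The 74% figure is back-solved and paired with perfect app feedback. At 90% control feedback the chance of a feedback-only significant result is small. This stands: the arithmetic shows possibility, not likelihood.
- **Component reporting is often left to an analysis plan.** True, but the outcome list is fixed in this article and does not contain the patient event alone.

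A reader might go further and infer that the app generates its own success, so that a positive trial would say nothing about women reaching care. The documents do not support that. By definition, a woman who never starts a procedure cannot count. Hospital nurses must operate the app. Its reminders are aimed at attendance and may truly raise it. The conclusion in the Abstract is also not tied to the primary outcome alone.

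**Conclusion.** The concern holds as one of interpretation. A significant primary result would be ambiguous between more women starting a procedure and better feedback for the same women; it would not be empty. A feedback gap alone can produce the full 52% versus 70% whenever the common procedure-start rate is at least 70%. With that rate at 70% and complete app feedback, the chance of significance runs from 0.76 at 74% control feedback to 0.19 at 90%. These figures rest on assumed feedback and procedure-start rates, an ICC of 0.01 and 35 women per cluster.

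Diagnosis within 60 days gives partial protection. The unequal ascertainment of procedure start adds to the difficulty. The point should be fixed because the remedy is cheap; it does not invalidate the primary analysis.

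**What to change.** 1. Keep the composite as the primary outcome.
2. Pre-specify a key secondary outcome: a first diagnostic or treatment procedure begun at the receiving institution no later than 60 days after referral, whether or not feedback arrived. Use the primary model, with all referred women as denominator.
3. Report feedback separately, among women who started a procedure, by arm.
4. State that claims about women reaching diagnosis rest on the patient-event outcomes: procedure start and diagnosis within 60 days.
5. Ascertain procedure start in the same way in both arms. Reconcile Participant timeline {13}, where intervention follow-up ends on arrival, with the definition in Outcomes {12}, and apply the 60-day receiving-facility record check of Plans for assessment {18a} to intervention women as well.

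The cost is one more secondary outcome, some wording, and a modest extension of record review. It should not be assumed that no new data are needed, because that review is described only for controls. Enrolment began on 30 November 2024 and the trial is unblinded, so the change should be made and dated before outcome data are examined by arm.
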